#### Preliminary analysis

The success of randomization to study group will first be examined. The groups will be compared on baseline demographics and clinical characteristics using analysis of variance (ANOVA) or χ^2^ tests as appropriate. Variables that differ, using α = 0.1 level of significance, across the study groups are potential confounders and will be adjusted for in all subsequent analyses.

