#### Analyses of Treatment Phase data

The primary hypothesis is that yoga is non-inferior to PT for our co-primary endpoints: reduction in back pain intensity and improvement in back-related function. First, a one-sided α = 0.05 level two-sample *t*-test will be used to determine if yoga is non-inferior to PT for the co-primary outcomes of pain and function. The mean differences between groups with corresponding standard errors, confidence intervals, and *P* values will be reported. While pain and RMDQ outcomes may have a tendency to be skewed, we are examining the change from baseline to week 12 in these scales as primary outcomes which are expected to have more normally distributed values. However, underlying assumptions of the *t*-test and regression models, including normality, will be examined. If important violations are found, then alternative methods will be explored including non-parametric methods. If any imbalance between groups is found in the preliminary analysis of the success of randomization, these variables will be used in regression models to adjust results, with change from baseline to week 12 with pain or function as the outcome, and treatment group and other potential confounders as predictors.

The following variables will be considered as possible effect modifiers for the relationship between treatment group and the outcomes of pain and function: study site, expectation of helpfulness, preference for treatment assignment, and depression. A multiplicative interaction term between treatment and the possible effect modifier of interest will be included in a regression model. If a significant interaction occurs, we will examine whether it is quantitative (e.g., two subgroups differ in the magnitude of effect, but the effect for both are in the same direction) or qualitative (i.e., two subgroups differ in the direction or interpretation of effect) in nature. We will also examine the secondary outcome of pain medication use during the previous week assessed at 12 weeks. Logistic regression with indicators for treatment and adjustment for possible confounders, including baseline medication use, will be used to compare medication usage rates between the yoga and PT groups. Medication subtypes including non-steroidal anti-inflammatory drugs, acetaminophen, opiates, muscle relaxants, and others will also be compared. Odds ratios with corresponding confidence intervals and *P* values will be reported.

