We also hypothesize that both the yoga and PT groups will show superior back-pain co-primary outcomes (pain reduction and back-related function) compared to the education group at 12 weeks. A two-sided α = 0.05 level two-sample *t*-test will be used to determine if yoga is superior to education for the co-primary outcomes of pain and function. Similarly, a two-sided α = 0.05 level two-sample *t*-test will be used to determine if PT is superior to education for the co-primary outcomes of pain and function. The mean differences between groups with corresponding standard errors, confidence intervals, and *P* values will be reported. If any imbalance between groups is found in the preliminary analysis of the success of randomization, these analyses will be adjusted using regression models with change from baseline to week 12 with pain or function as the outcome and treatment group or other potential confounders as predictors. For comparing pain medication use between the yoga, PT, and education intervention arms, we will use logistic regression as described above.

We will compare the following secondary outcomes using either linear or logistic regression, as appropriate, with treatment and potential confounders as predictors: overall improvement, patient satisfaction, and health-related quality of life.

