#### Sample size considerations

For the co-primary endpoints of change in pain or function from baseline to week 12, we assume a one-sided α error = 0.05. If we assume a minimal clinically significant difference of 2.0 points for the 11-point pain intensity scale, then using a 1.0 point non-inferiority margin for pain is reasonable [103]. If we assume 3.0 points on the 23-point RMDQ scale is a minimal clinical significant difference, then choosing a non-inferiority margin of 1.5 for function is reasonable [105]. A common standard deviation of change in all groups is 2.5 points for the 11-point pain intensity scale and 4.35 points for the 23-point RMDQ function scale [24,26].

Using these assumptions, 108 participants in both the yoga and PT group would provide 90% power to detect whether yoga is truly non-inferior to PT in respect to effect on pain. Similarly, 107 participants in both the yoga and PT group would provide 81% power to detect whether yoga is truly non-inferior to PT in respect to effect on function. Using these sample sizes, we would be able to detect at least a 1.4 unit difference in pain or at least a 2.4 difference in function with 90% power for superiority of yoga or PT compared to education. We inflated these sample sizes in order to protect against an estimated dropout rate of 20%. With this adjustment, the target sample size for the yoga and PT groups is 128 participants each. Using a yoga:PT:education 2:2:1 randomization scheme, we need a total of 320 participants (128 yoga, 128 PT, 64 education). Thus, for the co-primary outcomes of pain and function at 12 weeks, we have adequate power to determine non-inferiority between yoga and PT and superiority of yoga and PT to education*.*

We also anticipate adequate power for the longitudinal analyses of the Maintenance Phase data. Incorporation of repeated measures over time increases power by increasing the “effective sample size,” which is a function of the number of participants and the number of total measurements (0, 6, 12, 26, 40, and 52 weeks). Participants who drop-out or who have missing data can still be included in these analyses.

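### The 12-week primary comparison uses unadjusted change scores and adds covariates only when a baseline test at 0.1 flags them, rather than always adjusting for the outcome's own baseline score

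*Protocol article*

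**What the plan says.** All references are to the protocol article.

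- **Preliminary analysis.** The randomised groups are compared at baseline by ANOVA or chi-square tests. Variables that differ at the 0.1 level "across the study groups are potential confounders and will be adjusted for in all subsequent analyses".
- **Analyses of Treatment Phase data.** Yoga versus PT non-inferiority is tested first with a one-sided 0.05 two-sample t-test, and "we are examining the change from baseline to week 12 in these scales as primary outcomes". "If any imbalance between groups is found in the preliminary analysis of the success of randomization", the flagged variables go into a regression of the change score on treatment and those variables. The two superiority comparisons with education follow the same pattern with two-sided 0.05 t-tests.
- **Table 7 (Outcome measures).** Pain and RMDQ are both collected at baseline. Neither is a fixed covariate in the 12-week primary model. For the secondary outcome of pain medication use, by contrast, baseline use is named as a covariate.
- **Sample size considerations.** For the non-inferiority comparison, "we assume a one-sided α error = 0.05"; for pain, "then using a 1.0 point non-inferiority margin for pain is reasonable"; for function, "then choosing a non-inferiority margin of 1.5 for function is reasonable". "A common standard deviation of change in all groups is 2.5 points for the 11-point pain intensity scale and 4.35 points" for RMDQ. On this basis "108 participants in both the yoga and PT group would provide 90% power" for pain, and 107 per arm give 81% for function.

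**The concern.** Three features of the rule are unsatisfactory.

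1. **Selection by imbalance.** In a properly randomised trial, every baseline difference that passes the screen arose by chance. Passing it says nothing about whether the variable predicts the outcome. The screen also runs across all three arms, so a variable can be flagged because of the education arm and then enter the yoga–PT comparison.
2. **The most natural covariate is usually left out.** The baseline value of the outcome is normally among its best predictors. Here it enters only if it happens to be flagged, about one time in ten under randomisation.
3. **The decisive analysis is not named.** One section says flagged variables are adjusted for in everything that follows; another says the t-test determines non-inferiority and then adds a regression. If the two disagree about the margin, the text does not say which one counts.

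At stake are precision, chiefly for function, whose planned power is only 81%, and a primary model whose covariates cannot be listed before the baseline data are seen.

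**Working it through.** **Inputs from Sample size considerations:** one-sided α = 0.05 (z = 1.645); margins 1.0 (pain) and 1.5 (function); SD of change 2.5 and 4.35; n = 108 and 107 per arm. The true difference is taken as 0.

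**Inputs not in the documents, so assumed:** r, the correlation of baseline with week-12 score, 0.4 to 0.7; k, the ratio of baseline SD to week-12 SD, 1.0, 0.8 and 0.7.

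**Step 1: reproduce the plan's power.** Power = Φ(margin / [SD × √(2/n)] − 1.645).

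- Pain: 2.5 × √(2/108) = 0.340; 1.0/0.340 = 2.939; Φ(1.294) = 90.2%.
- Function: 4.35 × √(2/107) = 0.595; 1.5/0.595 = 2.522; Φ(0.877) = 81.0%.

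Both match the stated 90% and 81%.

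**Step 2: variance after adjusting for baseline.** With a common slope, and in units of the week-12 variance, the change score has variance 1 + k² − 2rk and the baseline-adjusted residual has variance 1 − r². The difference is (k − r)², which is never negative. The ratio is

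VR = (1 − r²) / (1 + k² − 2rk),

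which reduces to (1 + r)/2 when k = 1. The adjusted SD is the SD of change × √VR.

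**Step 3: power at the protocol's own n.**

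| k | r | VR | Pain, 108 per arm | Function, 107 per arm |
|---|---|---|---|---|
| unadjusted | – | 1 | 90.2% | 81.0% |
| 1.0 | 0.4 | 0.70 | 96.9% | 91.5% |
| 1.0 | 0.5 | 0.75 | 96.0% | 89.8% |
| 1.0 | 0.6 | 0.80 | 95.0% | 88.0% |
| 1.0 | 0.7 | 0.85 | 93.9% | 86.2% |
| 0.8 | 0.4 | 0.84 | 94.1% | 86.6% |
| 0.8 | 0.7 | 0.98 | 90.7% | 81.7% |
| 0.7 | 0.4 | 0.90 | 92.6% | 84.4% |
| 0.7 | 0.7 | 1.00 | 90.2% | 81.0% |

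Worked line (function, k = 1, r = 0.5): adjusted SD = 4.35 × √0.75 = 3.77; standard error = 3.77 × √(2/107) = 0.515; 1.5/0.515 = 2.912; Φ(1.267) = 89.8%.

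With equal variances the gain is about 4 to 7 points for pain and 5 to 10 for function. At k = 0.7–0.8 it is about 0 to 4 for pain and 0 to 6 for function.

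**Step 4: does the conditional rule recover the gain?** Simulated for function: 8,000 trials per setting, 107/107/53 participants, equal variances, with adjustment for baseline RMDQ only when the three-arm ANOVA gives p < 0.1.

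| r | t-test on change | Conditional rule | Always adjusted |
|---|---|---|---|
| 0.3 | 81% | 83% | 93% |
| 0.5 | 81% | 83% | 90% |
| 0.7 | 82% | 82% | 86% |

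The baseline score was flagged in about 10% of trials, so the rule recovers little of the gain. Type I error at the margin was about 4.8–5.1% for the t-test and 4.3–4.6% for the conditional rule.

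**Step 5: how often the screen fires.** For m independent baseline variables, P(at least one flag) = 1 − 0.9^m: 41% for m = 5, 65% for m = 10, 88% for m = 20. The documents give no count of tested variables, and real baseline variables are correlated, so these figures only illustrate that a flag is likely.

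**The case against.** The strongest defence is that nothing here is invalid. A t-test on change is unbiased under randomisation, the trial is sized with the matching SD of change, and the stated power reproduces. The screening rule is written in advance, is mechanical, and uses baseline data only, so it offers no route to choosing a model by its treatment result. Marked imbalance in baseline pain or RMDQ would be caught, because these count as clinical characteristics. All of this stands.

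The size of the gain is also uncertain. The simple factor (1 + r)/2 needs equal variances. Entry requires pain of at least 4, which truncates baseline pain but not week-12 pain, so a smaller baseline SD is plausible for pain and the gain could be close to nil. This stands too and is why the table shows several values of k.

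Stronger readings that a reader might infer are not supported:

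- **That the primary result is biased or its type I error inflated.** The simulation shows neither inflation from the change score nor from the conditional rule.
- **That regression to the mean from the pain entry threshold distorts the comparison.** The threshold applies to every arm and cancels on average; it matters only through chance baseline imbalance.
- **That adjustment is needed to rescue power among completers after dropout.** That concerns the dropout arithmetic, a separate matter, and the plan also carries last values forward. The comparison here uses the protocol's own 107–108 per arm.

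An article may leave a covariate list to an analysis plan. But the 0.1 screen and its use in all later analyses are stated here, so an analysis plan would have to overrule the published text, not merely complete it.

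**Conclusion.** The point holds as one of efficiency and of fixing the primary model. Covariates are selected by chance imbalance, the outcome's own baseline score is usually omitted, and the decisive analysis is not identified when something is flagged. These statements follow from the text and need no assumed correlation.

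The size rests on r and k, which the documents do not give. For r between 0.4 and 0.7, always adjusting raises function power from 81% to about 86–91% and pain power from 90% to about 94–97% if baseline and week-12 variances are equal. If the baseline SD is 0.7–0.8 of the week-12 SD, the gain is about 0–6 points. In large samples baseline adjustment is never less precise than the change score, so the choice carries essentially no risk. It is a worthwhile improvement that should be made, not the repair of an invalid test.

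**What to change.** For each co-primary outcome, pre-specify one primary linear model of the week-12 score (or the change score, which gives the same treatment estimate once baseline is in the model) with treatment and that outcome's baseline score as predictors. State that this model supplies the yoga–PT non-inferiority confidence interval and both superiority tests against education. Any further covariate should be named in advance for its prognostic value.

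Delete the 0.1 screening rule from Preliminary analysis and the conditional regression sentences from Analyses of Treatment Phase data, and report baseline comparisons descriptively. Keep the unadjusted t-test on change as a sensitivity analysis.

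The cost is wording only. Both baseline scores are already collected, no extra participants or visits are needed, and the sample size can stand. The article says the trial is still recruiting, so the change can be recorded before the outcome data are analysed.

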#### Analyses of Treatment Phase data

The primary hypothesis is that yoga is non-inferior to PT for our co-primary endpoints: reduction in back pain intensity and improvement in back-related function. First, a one-sided α = 0.05 level two-sample *t*-test will be used to determine if yoga is non-inferior to PT for the co-primary outcomes of pain and function. The mean differences between groups with corresponding standard errors, confidence intervals, and *P* values will be reported. While pain and RMDQ outcomes may have a tendency to be skewed, we are examining the change from baseline to week 12 in these scales as primary outcomes which are expected to have more normally distributed values. However, underlying assumptions of the *t*-test and regression models, including normality, will be examined. If important violations are found, then alternative methods will be explored including non-parametric methods. If any imbalance between groups is found in the preliminary analysis of the success of randomization, these variables will be used in regression models to adjust results, with change from baseline to week 12 with pain or function as the outcome, and treatment group and other potential confounders as predictors.

The following variables will be considered as possible effect modifiers for the relationship between treatment group and the outcomes of pain and function: study site, expectation of helpfulness, preference for treatment assignment, and depression. A multiplicative interaction term between treatment and the possible effect modifier of interest will be included in a regression model. If a significant interaction occurs, we will examine whether it is quantitative (e.g., two subgroups differ in the magnitude of effect, but the effect for both are in the same direction) or qualitative (i.e., two subgroups differ in the direction or interpretation of effect) in nature. We will also examine the secondary outcome of pain medication use during the previous week assessed at 12 weeks. Logistic regression with indicators for treatment and adjustment for possible confounders, including baseline medication use, will be used to compare medication usage rates between the yoga and PT groups. Medication subtypes including non-steroidal anti-inflammatory drugs, acetaminophen, opiates, muscle relaxants, and others will also be compared. Odds ratios with corresponding confidence intervals and *P* values will be reported.

We also hypothesize that both the yoga and PT groups will show superior back-pain co-primary outcomes (pain reduction and back-related function) compared to the education group at 12 weeks. A two-sided α = 0.05 level two-sample *t*-test will be used to determine if yoga is superior to education for the co-primary outcomes of pain and function. Similarly, a two-sided α = 0.05 level two-sample *t*-test will be used to determine if PT is superior to education for the co-primary outcomes of pain and function. The mean differences between groups with corresponding standard errors, confidence intervals, and *P* values will be reported. If any imbalance between groups is found in the preliminary analysis of the success of randomization, these analyses will be adjusted using regression models with change from baseline to week 12 with pain or function as the outcome and treatment group or other potential confounders as predictors. For comparing pain medication use between the yoga, PT, and education intervention arms, we will use logistic regression as described above.

We will compare the following secondary outcomes using either linear or logistic regression, as appropriate, with treatment and potential confounders as predictors: overall improvement, patient satisfaction, and health-related quality of life.

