**Yoga posture (**** *Asana)* **	**Classes incorporating posture by segment**				**Total classes incorporating posture**
	**Segment 1 weeks 1–3**	**Segment 2 weeks 4–6**	**Segment 3 weeks 7–9**	**Segment 4 weeks 10–12**	
	**Opening to something greater**	**Listening to the wisdom of the body**	**Engaging your power**	**Bringing it home**	
*Svasana* relaxation and breathing exercises	✓	✓	✓	✓	12
Knee to chest*	✓	✓	✓	✓	12
Knee together twist*	✓	✓	✓	✓	12
Pelvic tilt*	✓	✓	✓		9
Cat and cow pose (and modifications)*	✓	✓	✓		9
Chair pose (and modifications)*	✓	✓	✓		9
Shoulder opener*	✓	✓	✓	✓	12
Crescent moon (and modifications)*	✓	✓	✓		9
Mountain pose (and modifications)*	✓	✓	✓	✓	12
Chair twists, standing and seated	✓	✓	✓	✓	12
Child’s pose*	✓		✓	✓	9
Cobra (and modifications)*	✓	✓	✓	✓	12
Bridge pose* (with and without support)	✓	✓	✓	✓	12
Reclining cobbler*	✓	✓	✓		9
Downward facing dog (and at wall)*	✓	✓	✓	✓	12
Triangle pose (with and without the wall)		✓	✓	✓	9
Locust pose*	✓	✓			6
Sphinx*		✓	✓	✓	9
Standing forward bend at wall*		✓	✓	✓	9
Warrior pose*			✓	✓	6
Extended leg pose*		✓	✓	✓	9
Sun salutations				✓	3
Baby dancer pose*				✓	3
Spinal rolls				✓	3
*Svasana* integrative relaxation	✓	✓	✓	✓	12

The hatha yoga protocol developed for chronic low back pain patients consists of 12 weekly 75-min yoga classes divided into four 3-week segments. Each segment has a theme. The exercises for each segment are indicated in the table. Each class begins and ends with a relaxation exercise. The protocol provides for modifications of poses to accommodate different abilities.

*Exercises included in the DVD provided to participants for home practice.

Classes usually have 1–3 yoga teachers and no more than 4–5 participants per yoga teacher. This ensures adequate individual attention from the teacher, maximizes safety and effectiveness, and allows flexibility in yoga teacher scheduling based on the study’s needs. In the event that only one or two participants appear for a given class, the class still occurs and is not cancelled. In the event of unusual or extenuating circumstances (e.g., a participant misses multiple classes due to an emergency), we may attempt to set up a special make-up individual class so the participant can “catch up” and successfully rejoin his or her group class as soon as possible. However, these are rare; one-on-one instruction in the yoga group is not planned or routine.

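### The 12-week t-tests and the sample size ignore yoga class; if outcomes correlate within class, the non-inferiority error rises above 5% and the stated power is too high

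*Protocol article*

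**What the plan says.** The Hatha yoga section describes a weekly group class with one to three teachers and "no more than 4–5 participants per yoga teacher". Participants belong to a group class that they rejoin after absences, individual teaching is exceptional, and classes are organised in cohorts. Physical therapy (PT) is given one to one at two private-network sites and a hospital department (Study sites; Physical therapy). Education is a book with newsletters.

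Under Analyses of Treatment Phase data, a one-sided two-sample t-test on change to week 12 "will be used to determine if yoga is non-inferior to PT for the co-primary outcomes of pain and function". Two-sided two-sample t-tests compare yoga and PT with education. Regression adjustment is reserved for variables found imbalanced at baseline, and study site enters only as a possible effect modifier. The Maintenance Phase model handles only the correlation among one person's repeated measures.

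Under Sample size considerations, "we assume a one-sided α error = 0.05", "using a 1.0 point non-inferiority margin for pain is reasonable" and "choosing a non-inferiority margin of 1.5 for function is reasonable". The planning assumption for spread reads "A common standard deviation of change in all groups is 2.5 points" on the pain scale; the corresponding figure on the function scale is 4.35. No ICC or design effect appears.

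**The concern.** People who share a class for 12 weeks share teachers, peers, place and timetable, so their outcomes may be more alike than those of two participants picked at random. Education participants share no sessions, and PT participants share at most a therapist. This is a partially nested design.

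A two-sample t-test estimates the variance of the yoga mean as if every participant were independent. With a positive within-class correlation that estimate is too small. In a non-inferiority comparison the direction matters: an interval that is too narrow clears the margin too easily, so yoga could be declared non-inferior more often than the stated 5% allows. The yoga-versus-education test errs the same way. Planned power is overstated too, because the sample size rests on the same independence.

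**Working it through.** **Inputs from Sample size considerations.** One-sided α 0.05 (z = 1.645); margins 1.0 (pain) and 1.5 (function); standard deviations of change 2.5 and 4.35; 108 per arm for 90% power on pain; 107 per arm for 81% power on function.

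**Input from Hatha yoga.** One teacher with up to 5 participants gives a class of about 5. Three teachers with 5 each gives the ceiling of 15.

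**Assumed.** ICC 0.01 to 0.05, because the document gives none; clustering in the yoga arm only; equal class sizes.

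**Step 1. Reproduce the stated power.** With independent observations and a true difference of zero, power = Φ(margin / (SD × √(2/n)) − 1.645).

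- Pain: 1.0 / (2.5 × √(2/108)) = 2.939; Φ(2.939 − 1.645) = 90.2%.
- Function: 1.5 / (4.35 × √(2/107)) = 2.522; Φ(2.522 − 1.645) = 81.0%.

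Both match the stated 90% and 81% with no design effect, so the planned numbers contain no allowance for clustering.

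**Step 2. Error rate of the unadjusted test.** Yoga-arm design effect DE = 1 + (m − 1) × ICC for m per class. With equal arms the variance of the yoga–PT difference is inflated by V = (DE + 1)/2. True one-sided error = 1 − Φ(1.645/√V).

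| Per class | ICC | DE | V | √V | True error |
|---|---|---|---|---|---|
| 5 | 0.01 | 1.04 | 1.020 | 1.010 | 5.2% |
| 5 | 0.05 | 1.20 | 1.100 | 1.049 | 5.8% |
| 10 | 0.01 | 1.09 | 1.045 | 1.022 | 5.4% |
| 10 | 0.02 | 1.18 | 1.090 | 1.044 | 5.8% |
| 10 | 0.05 | 1.45 | 1.225 | 1.107 | 6.9% |
| 15 | 0.01 | 1.14 | 1.070 | 1.034 | 5.6% |
| 15 | 0.05 | 1.70 | 1.350 | 1.162 | 7.8% |

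A simulation of the plain t-test at the function margin (107 per arm, 40,000 runs per scenario) agrees: 6.9% at 10 per class and ICC 0.05, 7.9% at 15 per class and ICC 0.05, and about 5% at ICC 0.

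**Step 3. Power with a correct standard error, at the stated numbers.** Divide the Step 1 ratios by √V. At 10 per class and ICC 0.05 (√V = 1.107):

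- Pain: Φ(2.939/1.107 − 1.645) = 84%.
- Function: Φ(2.522/1.107 − 1.645) = 74%.

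Recovering the stated power there would take 108 × 1.225 = 132.3, so 133 analysed per arm for pain, and 107 × 1.225 = 131.1, so 132 for function. These are normal approximations. About 11 classes (107/10) leave few degrees of freedom, so exact power would be slightly lower.

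**Step 4. Yoga versus education.** With about 107 and 53 analysed (the 2:1 ratio), V = (1.45/107 + 1/53) / (1/107 + 1/53) = 1.149 at 10 per class and ICC 0.05. The two-sided error is 2 × (1 − Φ(1.96/√1.149)) = 6.7%. PT versus education is untouched by yoga class.

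**The case against.** Several points on the other side stand.

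- **The ICC is unknown.** A reader might infer that the standard errors are too small and the error rate does exceed 5%. The document does not establish that: at ICC 0 the test holds its level, and in classes of 5 at ICC 0.01 the excess is 0.2 percentage points.
- **Fifteen is a ceiling.** One-teacher classes of 5 or fewer are allowed, and there the error is 5.2% to 5.8% over the assumed ICC range. The 7.8% needs every class full and the highest assumed ICC.
- **PT cannot be sized.** It is tempting to add a therapist effect of the same size and quote an error of 10% or more. The document names three locations but gives neither a number of therapists nor a caseload, so such figures have no basis in it.
- **Power at about 102 per arm would be the wrong comparison.** Removing 20% of 128 mixes in a separate dropout question. The primary analysis carries last values forward, so up to 128 per arm could be analysed. At 128, with 10 per class and ICC 0.05, power is Φ(3.2/1.107 − 1.645) = 89% for pain and Φ(2.759/1.107 − 1.645) = 80% for function, close to the stated figures. But those extra participants were added to cover dropout, not clustering, and a larger n does nothing for the error rate of the unadjusted test.
- **The common standard deviation is a planning assumption.** It does not show that a pooled-variance t-test will be used.

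The argument that this is detail left to the analysis plan does not stand. The article itself fixes the test and the sample size. It promises to check model assumptions, but it names normality and, as a fallback, non-parametric methods; the standard ones also assume independent participants.

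**Conclusion.** The point holds in conditional form. The 12-week t-tests and the sample size treat yoga participants as independent although they are taught in stable groups. If the within-class ICC is positive, the non-inferiority interval is too narrow and the stated power too high. With yoga-only clustering, 5 to 15 per class and an assumed ICC of 0.01 to 0.05, the one-sided error is about 5.2% to 7.8%. At 10 per class and ICC 0.05 it is about 6.9%, with power at the stated 107 to 108 analysed per arm of about 84% for pain and 74% for function. Any therapist effect in the PT arm adds to this by an amount the document does not let one calculate. The effect is modest but favours the trial's primary claim, and it is cheap to remove.

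**What to change.** - For the 12-week non-inferiority and superiority comparisons, replace the plain t-test with a partially nested mixed model: random intercept for yoga class or cohort in the yoga arm, arm-specific residual variances, and small-sample degrees of freedom (Satterthwaite or Kenward–Roger). Cluster-robust standard errors with a small-sample correction are an acceptable alternative.
- Add a random intercept for therapist in the PT arm where the therapist is recorded, at least as a sensitivity analysis.
- Restate power over an assumed ICC range, leaving the sample size unchanged.
- In the longitudinal analysis, use the Treatment Phase class only in a sensitivity analysis. Maintenance yoga is drop-in and the no-maintenance groups attend no study classes, so one class intercept does not describe the period after week 12.

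The change is to analysis text, plus confirming that each participant's class, and therapist where possible, is recorded. The article says recruitment is under way, so this can be fixed before outcomes are analysed. The cost is slightly wider intervals and lower stated power.
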